### Sample size

The sample size calculation is based on an ANCOVA for the primary outcome zBMI at 12 months, using the baseline zBMI as a covariate. The total sample size of 108 (54 per arm) is based on the following criteria: a two-sided, level 0.05 test of the null hypothesis of no difference; power of 0.80; smallest clinically important difference is 0.5 zBMI units at 12 months; between-subject standard deviation is 1 unit; and within-subject correlation is 0.638, derived from TARGetKids! dataset of subjects meeting criteria (*n* > 700). Lost-to-follow-up is estimated at 10% [26, 27]. Obesity intervention trials in young children with 15–50 children per group have demonstrated significant treatment effect sizes of 0.3–0.5 units of zBMI [10].

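### The stated ANCOVA inputs give 86–88 enrolled participants, not 108, so the stated power of 0.80 does not belong to this sample size

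*Protocol article*

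**What the plan says.** The Sample size section of the protocol article names the method: "The sample size calculation is based on an ANCOVA for the primary outcome zBMI at 12 months, using the baseline zBMI as a covariate". It then gives the result and its basis: "The total sample size of 108 (54 per arm) is based on the following criteria: a two-sided, level 0.05 test". The listed inputs are:

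- Test: two-sided, at the 0.05 level
- Power: 0.80
- Difference to be detected: "smallest clinically important difference is 0.5 zBMI units at 12 months"
- Spread of the outcome: an SD of 1
- Link between baseline and follow-up values: "within-subject correlation is 0.638, derived from TARGetKids! dataset of subjects meeting criteria"

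After these comes "Lost-to-follow-up is estimated at 10" per cent, without saying whether 108 is the number before or after that loss. Allocation is 1:1 (Study design). The section on statistical analysis of clinical data also specifies ANCOVA for the primary outcome, adjusted for baseline zBMI, age and five risk indicators. The article mentions no inflation for clustering or any other allowance.

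**The concern.** Every quantity that a two-arm ANCOVA sample size needs is printed, so the result can be checked directly, and it does not follow. The stated total is about a quarter larger than the inputs require, which is too much for rounding.

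Two explanations are possible, and they have different consequences. If the inputs are right, power at 0.5 is well above 0.80 and the trial has 80% power for a smaller difference than 0.5. That bears on how a null result is read, since the same section cites earlier trials with effects of 0.3–0.5 zBMI units. If 108 came from another formula, or from an allowance that is not disclosed, then the stated method or inputs are not the ones the sponsor relied on. The text does not show which explanation applies.

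**Working it through.** **Inputs** (all from Sample size, except 1:1 allocation from Study design): difference 0.5; SD 1; correlation 0.638; two-sided level 0.05; power 0.80; loss 10%.

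**Attempt to reproduce 108**

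1. Residual variance under ANCOVA: 1 − 0.638² = 1 − 0.407 = 0.593.
2. Normal formula, per arm: 2 × (1.960 + 0.842)² × 0.593 / 0.5² = 2 × 7.849 × 0.593 / 0.25 = 37.2, so 38 per arm, 76 evaluable.
3. Noncentral t with 2n − 3 degrees of freedom: n = 38 gives power 0.798 and n = 39 gives 0.808, so 39 per arm, 78 evaluable.
4. Allowing for 10% loss: 38/0.9 = 42.2, so 43 per arm (86); 39/0.9 = 43.3, so 44 per arm (88).
5. Gap to the stated total: 108 − 88 = 20, or 108 − 86 = 22.

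The additional covariates planned for the primary analysis do not close the gap. Charging six more degrees of freedom lowers power at n = 39 from 0.808 to 0.807.

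**What 108 gives under the stated inputs** (noncentral t)

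| Reading of 108 | Evaluable per arm | Power at 0.5 | Difference with 80% power |
|---|---|---|---|
| Enrolled, 10% then lost | 54 × 0.9 = 48.6 | 0.886 | 0.442 |
| Evaluable | 54 | 0.917 | 0.419 |

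The normal approximation gives 0.893 and 0.438 in the first row, and 0.921 and 0.415 in the second. On the second reading, enrolment would have to be 108/0.9 = 120.

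**Other formulas, two-sided 0.05, with 10% loss**

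| Formula | Per arm, evaluable | Total enrolled |
|---|---|---|
| Unadjusted comparison at 12 months, power 0.80 | 63–64 | 140–144 |
| ANCOVA, power 0.90 | 50–51 | 112–114 |
| Change from baseline, variance 2(1 − 0.638) = 0.724, power 0.80 | 46 (normal), 47 (t) | 104 or 106 |

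For the change score, 46/0.9 = 51.1, so 52 per arm; 47/0.9 = 52.2, so 53 per arm. This is the nearest to 54, but it does not reach it.

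**What would have to differ for ANCOVA to give 54 enrolled per arm at 80% power**, one input at a time: a correlation of about 0.49 (t) or 0.475 (normal) instead of 0.638; or an SD of about 1.13–1.14 instead of 1; or a loss of about 28–30% instead of 10%. Each contradicts the text.

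**The case against.** The strongest reply is that the error is harmless. On either reading of the 10%, 108 exceeds what the stated power requires. The article presents 0.5 as the smallest important difference, not as the smallest detectable one, and a null result would be read mainly from the planned mean difference and confidence interval. This stands as far as it goes: the trial is not underpowered on its stated inputs, and the weight of the point should reflect that. It does not make 0.80 the right power for 108.

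A second reply is that the inputs may be right and only the formula misnamed. A t-based change-score calculation comes within two participants of 108. This is plausible but remains inference. It gives 53 per arm, not 54, and the article names ANCOVA for both the sample size and the analysis. If a change-score formula was used, the section names the wrong method and still needs correcting.

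A third reply is that a condensed article may leave out an allowance given in the full protocol, for example for group-delivered sessions. That is fair, and it is a reason not to print a higher power before checking. As an illustration with assumed values, inflating the variance by 1.25 at 48.6 per arm lowers power from 0.886 to about 0.81, and inflating it by 1.3 lowers it to about 0.79. But condensation does not account for the mismatch itself: the article presents 108 as the result of the criteria it lists.

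**Conclusion.** The point holds. Taken literally, the inputs give 76–78 evaluable and 86–88 enrolled participants, against 108 stated. At 108, power for 0.5 zBMI is about 0.89 with 10% loss and 0.92 without, not 0.80. These figures rest on the article's own SD, correlation, difference and loss, on 1:1 allocation, and on independent outcomes within each arm. The discrepancy is in the conservative direction. It is a reporting error that should be corrected, and it gives no reason to change recruitment. Which formula or allowance actually produced 108 cannot be settled from the article.

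**What to change.** First, retrieve the calculation behind 108, and state in the Sample size section the formula used, any allowance beyond the listed inputs, and whether 108 is the number randomized or the number analysed.

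- If no other input was used and 108 is the number randomized, keep it and restate: 108 randomized, 10% loss, about 97 analysed (108 × 0.9 = 97.2), giving about 89% power for a difference of 0.5 zBMI and 80% power for 0.44.
- If another formula or a variance inflation was used, name it, give its value and show the calculation, so that 108 and the stated power follow from the text.
- If 108 is the number analysed, say so and give the enrolment target of 120.

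The cost is one paragraph of text. In the first two cases enrolment does not change.

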#### Feasibility and acceptability

Semi-structured interviews will be conducted with parent participants in the intervention and control groups to assess their experiences with the intervention, perceived quality of the intervention, and barriers and facilitators to their participation. Interviews will be recorded and transcribed, and thematic analysis will be conducted.

Fidelity to the core components of the intervention will be measured by the public health nurses following each group session and coaching visit using fidelity checklists and reported using descriptive statistics.

#### Economic evaluation analysis

Cost-effectiveness will be expressed as the incremental cost-effectiveness ratio (ICER) calculated by dividing the incremental costs between the intervention and usual care arms by the incremental change in the child’s zBMI between baseline and the end of the follow-up period. A probabilistic analysis using Monte Carlo simulation will be used to establish a point estimate and 95% confidence interval of the ICER. Extensive sensitivity analysis will be used to examine the robustness of the results and evaluate uncertainty in each of the parameters in the analysis. Ranges for the sensitivity analysis will be obtained from 95% confidence intervals generated from study data for each of the parameters. This analysis will be conducted in accordance with guidelines set out by the Canadian Agency for Drugs and Technologies in Health [28].

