Family psychosocial health (baseline and 6- and 12-month follow-up)	Mental health	**Depression, Anxiety, Stress Scale (DASS-21)** The *DASS-21* is a 21-item parent-completed form designed to measure the negative emotional states of depression, anxiety, and stress. Each of the three DASS scales contains 7 items per scale [49] **Parenting Stress Index (PSI)** The 36-item, parent-completed PSI is designed to identify potentially dysfunctional parent–child systems and includes three scales: parental distress, difficult child characteristics, and dysfunctional parent–child interaction [50] **Patient Health Questionnaire (PHQ-9)** The Patient Health Questionnaire (PHQ-9) [51] is a self-administered multipurpose instrument for monitoring and measuring the severity of depression. The inventory scores each of the nine DSM-V criteria for depression as “0” (not at all) to “3” (nearly every day), and scores of 5, 10, 15, and 20 represent mild, moderate, moderately severe, and severe depression
Healthcare utilization	Total and mental health-related ED visits and hospitalizations for children and mothers	The study data will be linked to ICES, to gain access to information such as CIHI databases, specifically the Discharge Abstract Database (DAD) for hospitalizations and the National Ambulatory Care Reporting System (NACRS) for emergency visits for the purpose of identifying early life exposures in this cohort
Feasibility and acceptability		Semi-structured interviews with parents to assess their experiences of the overall conduct of the trial, perceived quality of the intervention, and barriers and facilitators to participation
Fidelity to the intervention		Fidelity checklists of core components for each group session and coaching visits will be completed by the public health nurses
Economic evaluation (12-month follow-up)		Cost-effectiveness will be expressed as the incremental cost-effectiveness ratio (ICER), which will be calculated by dividing the incremental costs between the treatment and control arms by the incremental change in the child’s zBMI between baseline and the end of the follow-up period

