### Statistical analysis of clinical data

Appropriate descriptive statistics for baseline characteristics (frequencies and proportions for discrete variables; means and standard deviations for symmetric variables; and medians and inter-quartile ranges for skewed data) will be used to compare groups. The principle of intention-to-treat will be applied to the analysis of outcomes. Outcome variables will be compared between arms using ANCOVA with the corresponding baseline measure as the covariate. For the primary outcome, the following additional covariates will be included: age and each of the risk indicators—(i) birth weight greater than 3500 g, (ii) weight gain in the first year of life, (iii) maternal or paternal obesity, (iv) smoking during pregnancy, and (v) mean family income less than $80,000. Mean differences and corresponding confidence intervals will be calculated. A two-sided level of 0.05 will be applied for the primary outcome. To determine if the treatment effect on the primary outcome depends on baseline BMI, the interaction term between the treatment group and baseline BMI will be added to the covariate model. If this term is significant at the 0.1 level, then sub-groups determined by baseline BMI will be examined.

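### The planned 95% confidence interval for the ICER cannot be interpreted when the interval for the zBMI difference includes zero, which is likely at this sample size unless the effect is near 0.5

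*Protocol article*

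**What the plan says.** Under Economic evaluation analysis, the protocol article expresses cost-effectiveness as an ICER: the cost difference between arms divided by "the incremental change in the child’s zBMI between baseline and the end of the follow-up period". Table 1 defines the denominator in the same way. Uncertainty is to be shown on the ratio itself: "A probabilistic analysis using Monte Carlo simulation will be used to establish a point estimate and 95% confidence interval of the ICER". The section adds sensitivity analyses over parameter ranges and conformity with a national guideline that is not reproduced.

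The clinical effect is handled under Statistical analysis of clinical data: "Outcome variables will be compared between arms using ANCOVA with the corresponding baseline measure as the covariate". For zBMI, age and five risk indicators are added to the model.

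The Sample size section gives 54 per arm, SD 1, within-subject correlation 0.638, 10% loss to follow-up and a target difference of 0.5. It adds that earlier small trials "have demonstrated significant treatment effect sizes of 0.3–0.5 units of zBMI".

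**The concern.** A ratio with an uncertain denominator behaves badly near zero. Suppose the intervention costs more. As the simulated zBMI benefit shrinks towards zero, the ratio rises without limit. Once the benefit becomes a harm, the ratio jumps to a very large negative value. Two almost identical draws then sit at opposite ends of the ordered list, and costlier-and-worse draws rank below the most favourable positive ratios. If the cost difference can also be negative, a negative ratio may equally mean cheaper and better. Limits taken at the 2.5th and 97.5th percentiles of such a list cannot be read as a range of cost-effectiveness.

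The Knowledge translation section names policy-makers among the intended users of the findings. The Background cites two primary-care trials with no zBMI benefit and two other trials with small reductions, so an effect well below 0.5 is a credible outcome.

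**Working it through.** **Inputs.** All design inputs are from the Sample size section. Expected completers per arm are 54 × 0.9 = 48.6. The article gives no ICER or cost figure to reproduce, so every cost below is an assumption, in unspecified currency units. The effect d is the zBMI reduction in favour of the intervention. Cost and effect draws are taken as independent and normal.

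The stated ANCOVA inputs give 2 × (1.96 + 0.842)² × 0.593 / 0.5² = 37.2, so 38 per arm, or 43 after 10% loss, rather than 54. That is a separate matter. The stated 54 is used here.

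**Step 1: precision of the denominator.**
- ANCOVA variance factor: 1 − 0.638² = 0.593.
- SE = √(2 × 0.593 / 48.6) = 0.156.
- The 95% interval includes zero whenever the observed difference is smaller than 1.96 × 0.156 = 0.306. With normal draws centred on the estimate, this is the same as more than 2.5% of draws having the opposite sign.

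**Step 2: how often this happens.** P(interval includes 0) = Φ(1.96 − δ/SE) − Φ(−1.96 − δ/SE), where δ is the true effect.

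| True effect δ | δ/SE | P(interval includes 0) |
|---|---|---|
| 0.5 | 3.20 | 11% |
| 0.3 | 1.92 | 52% |
| 0.2 | 1.28 | 75% |
| 0 | 0 | 95% |

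If all 54 per arm completed, SE would be 0.148 and the figures 8% at 0.5, 47% at 0.3 and 95% at 0.

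**Step 3: what the planned interval then looks like.** Assume a cost difference of 1000 with SE 200.
- Observed effect 0.5: Φ(−3.20) = 0.07% of effect draws fall at or below zero. The percentile interval is about 1,000 to 5,400, which is usable.
- Observed effect 0.3: Φ(−1.92) = 2.7% fall at or below zero. The percentile interval is about −6,600 to 21,600.

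With the cost SE held at one fifth of the cost, the limits scale with cost. At an observed effect of 0.3 they are about −3,300 to 10,800 for a cost of 500 and −9,900 to 32,400 for a cost of 1500.

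**Step 4: comparison with the Fieller set** (effect 0.3, cost 1000, SE 200). The set holds all R with (d² − 1.96²SE²)R² − 2cdR + (c² − 1.96²SE_c²) ≤ 0.
- Leading coefficient: 0.0900 − 0.0937 = −0.0037, so the set is unbounded.
- Constant: 1,000,000 − 153,664 = 846,336.
- Roots: about 1,400 and −161,800. The set is every R above 1,400 together with every R below −161,800.

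The percentile interval therefore includes values from −6,600 to 1,400 that the data reject, and leaves out values above 21,600 that they do not.

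**Step 5: mixed meanings.** With cost 1000, SE 500 and effect 0.3, 4.9% of ratios are negative: 0.0274 × 0.977 = 2.7% costlier and worse, and 0.0228 × 0.973 = 2.2% cheaper and better.

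**Step 6: coverage.** The percentile interval was simulated with 48 completers per arm, cost 1000 and SE 200 or 500. Coverage is 96–98% for true effects of 0.1 to 0.5, 91–92% at 0.05, 66–74% at 0.02, 20–26% at 0.01 and about zero at 0.005.

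**Step 7: the denominator wording.** An unadjusted change-score difference has variance factor 2(1 − 0.638) = 0.724. The ratio to ANCOVA is 0.724 / 0.593 = 1.22, and the SE is 0.173. The chance that the interval includes zero would be 17% at 0.5 and 59% at 0.3.

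**The case against.** The strongest reply has four parts.

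1. The interval works at the design effect, and coverage is near nominal for true effects of 0.1 or more. This stands. A reader might infer that the interval is invalid as soon as any draw can cross zero, but the article's inputs do not support that. Normal draws can always cross; what matters is how often. Above about 0.1 the defect is one of interpretation, and only close to zero is coverage lost.

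2. A reader might infer that the economic analysis uses raw change scores in place of the trial's adjusted effect. The article does not say so. It refers to change in "zBMI between baseline and the end of the follow-up period" without saying whether that change is adjusted. With baseline as a covariate, ANCOVA on change and ANCOVA on the 12-month value give the same treatment coefficient. Even an unadjusted difference targets the same quantity under randomisation. This part is a request for clarification.

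3. The article condenses a fuller protocol and cites a guideline, so the cost-effectiveness plane, net benefit and acceptability curve may be specified elsewhere. Their absence is not the point. The point is the output that the article does commit to.

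4. The analysis is not primary, and all cost figures are assumed. Both are true. The probabilities in Step 2 do not depend on cost, and the pattern at 0.3 is the same across the assumed costs.

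**Conclusion.** The concern holds conditionally. The stated method gives an uninterpretable result whenever the 95% interval for the zBMI difference includes zero. On the design inputs that is about one trial in nine at a true effect of 0.5, about half at 0.3 (the low end of the range the article cites), and 95% at no effect. If the observed effect is near 0.5, the planned interval is serviceable. These figures assume SD 1, correlation 0.638, 10% loss, normal draws and no precision gain from the extra covariates. The illustrative intervals also rest on assumed costs of 500 to 1500.

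The denominator is not shown to be wrong. If it were an unadjusted change-score difference, the cost would be about 22% more variance and a possible mismatch with the published primary estimate, without bias.

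**What to change.** Replace the commitment to a Monte Carlo confidence interval of the ICER with the following:
- incremental cost and incremental zBMI effect, each with its own 95% interval;
- the joint simulated draws on the cost-effectiveness plane;
- net benefit with an acceptability curve over a stated range of willingness-to-pay per zBMI unit;
- an ICER interval, for example by Fieller's method, only when the effect interval excludes zero.

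Add one sentence stating that the ICER denominator is the baseline-adjusted zBMI difference at 12 months from the primary model.

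The cost is a change of wording and some extra figures, with no new data collection. The drawback is that a willingness-to-pay range must be chosen and shown, and the article gives no threshold per zBMI unit. Using the adjusted effect improves precision but does not remove the problem, so the change in reporting is needed in either case.

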### Parent-oriented research approach

Parents participating in the TARGetKids! network have reviewed and provided feedback on the proposed study protocol and recruitment methods via a Parents’ Panel [29]. The Parents’ Panel was developed to engage parents involved in TARGetKids! research and gather their perspectives on proposed ongoing research. The Parent Panel will be engaged throughout the trial to support the interpretation of results and knowledge translation.

### Knowledge translation

TARGetKids! is a collaboration between child health researchers, primary care practitioners (pediatricians and family physicians), parents, and their children. This study incorporates an integrated knowledge translation approach through continuous engagement with practicing primary care clinics and public health nurses in the TARGetKids! network and with parents. At end-of-grant, study findings will be communicated to key knowledge users including parents, health professionals and organizations (primary care physicians and public health practitioners), decision- and policy-makers, and other researchers. The research team will actively engage with policy-makers early in the execution of the trial to ensure the program is scalable and feasible from a health policy perspective. Reporting of outcomes in peer-reviewed manuscripts will be guided by STaRI standards [30].

## Discussion

There are a few practical and operational issues that have been taken into consideration throughout the conduction of this trial. There have been challenges with coordinating the group sessions, to find a time that is appropriate for all parents attending these sessions. Due to COVID-19, the group sessions transitioned to online delivery which may have allowed an increase in program attendance. Recruitment into the trial was delayed due to COVID-19, as the primary method for recruitment is conducted in clinical practice. Participant uptake of coaching calls has also posed a challenge, as some participants are not always interested in attending these calls. To mitigate this, we have not made the coaching calls mandatory but encouraged by the public health nurse. One last challenge in terms of recruitment for this trial is the eligibility criteria. Participants included in this trial are those that have children who are at risk of developing obesity, which may present as a sensitive topic to discuss with a participant (parent) during initial enrolment. To aid in this discussion, we have implemented a script to guide our research assistants when communicating with the parent surrounding the topic of weight bias.

## Trial status

Protocol version number and date: 05 Jan 2021

Start date of recruitment: May 1, 2018

Estimated completion date of recruitment: April 15, 2023

## Data Availability

The final trial dataset will be available to study investigators and the Research Ethic Boards at all participating sites. The datasets analyzed during the current study and statistical code are available from the corresponding author on reasonable request, as is the full protocol.

